#### Phase IIb procedures

2.4.2

The primary objective of Phase IIb is to evaluate the preliminary efficacy of OSanDiaBé in improving dietary adherence (primary behavioral outcome), and glycemic control (HbA1c) (primary biomedical outcome), as well as related T2D risk factors. Prior to study initiation, intervention materials will be finalized based on feedback from Phase IIa while preserving the core dietitian-led MNT framework. Facilitators will receive standardized training and lesson plans to ensure implementation fidelity.

As outlined in Table 2, participants in the intervention group will attend four individual sessions (45–60 min each) and eight group sessions (90–120 min each) during the first 6 months. The first two individual sessions will be delivered before and after the group sessions within the initial 3 months, followed by 2 monthly booster sessions between months 3 and 6. Group sessions will be delivered weekly or biweekly over an eight-week period. Intervention participants will receive the OSanDiaBé resource package, including a participant workbook, and an individualized Eating Plan based on the 4A food security framework. No intervention contact will occur between months 6 and 12. Participants in the wait-list control group will complete assessment visits at baseline, 3 months, 6 months, and 12 months and will receive usual care during the study period. Following completion of the 12-month assessment, they will be offered the OSanDiaBé intervention delivered by the same trained facilitators to ensure equitable access.

**Table 2 T2:** Overview and timeline of the OSanDiaBé intervention and assessments (ORBIT Phase IIb).

**Study activities**	**Baseline (Month 0)**	**3 months (End of Core Delivery)**	**6 months (End of Active intervention)**	**12 months (Maintenance Follow-up)**
Enrollment, informed consent, and randomization	X			
Usual care (control group; standard clinical management throughout study)	X	X	X	X
Individual MNT sessions (*n* = 4; intervention group)	X	X	X	
Group MNT sessions (OSanDiaBé; *n* = 8; intervention group)		X (Months 0–3)		
Dietary assessments (e.g., dietary adherence, diet quality/intake screener)	X	X	X	X
Psychosocial assessments (family functioning, self-efficacy, diabetes knowledge, quality of life)	X	X	X	X
Anthropometric measurements (weight, height, BMI, waist circumference)	X	X	X	X
Metabolic assessments (HbA1c, blood pressure, lipid profile)	X	X	X	X

The active intervention phase spans Months 0–6. Core group-based OSanDiaBé sessions (n = 8) and the first two individual MNT sessions are delivered during Months 0–3. Two monthly booster individual MNT sessions are delivered during Months 3–6. The maintenance phase (Months 6–12) involves no intervention contact and includes follow-up assessments only.

Outcome assessments for both groups will be conducted at baseline and at 3, 6, and 12 months. Dietary adherence will be assessed using a multi-method approach combining the PDAQ adapted to the Benin Food Guide, dietary intake from the modified UKDDQ, and facilitator-based behavioral monitoring, consistent with the Phase IIb measurement strategy (50, 51, 53). Secondary outcomes will include: diabetes knowledge assessed using the ADKnowl questionnaire (55); family functioning measured with the 12-item General Functioning subscale of the Family Assessment Device (54); nutrition self-efficacy assessed using the DSES (56); and quality of life measured with the EuroQol EQ-5D (59). Anthropometric measures (weight, height, body mass index, waist circumference) and metabolic indicators (blood pressure, HbA1c, lipid profile) will be collected, with venous blood samples analyzed at an accredited hospital laboratory. In addition, focus group discussions with participants and facilitators will be conducted at 3, 6, and 12 months to capture experiential feedback related to intervention delivery, cultural relevance, and perceived impact, and to inform future program refinement.

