#### Phase IIa procedures

2.3.2

Participants will complete two individual sessions—one prior to and one following the group sessions—and eight group sessions delivered weekly or biweekly over a 6–8-week period (Figure 3). The initial individual session will last approximately 60 min, followed by a 45–60-minute follow-up session. Prior to the first visit, dietitians will collect relevant medical history and laboratory data. During the initial session, dietary intake will be assessed using the modified UK Diabetes and Diet Questionnaire (UKDDQ) to inform individualized nutrition prescriptions (50). Throughout the intervention, facilitators will monitor behavioral changes related to meal planning, food preparation, and physical activity, using a standardized adherence scale ranging from 1 (never) to 5 (consistently) (51). Family members will be invited to selected group sessions, including introductory and healthy-eating sessions, to promote a supportive home environment and reinforce family-centered dietary practices.

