**Figure 3 F3:**
[figure not shown]
Schematic diagram of the feasibility study for the new cultural tailored medical nutrition therapy.

To support future replication and scalability, feasibility and acceptability outcomes will be evaluated using the RE-AIM (Reach, Effectiveness, Adoption, Implementation, and Maintenance) framework (52). Feasibility indicators will include recruitment strategies, session attendance, retention rates, and facilitator fidelity assessed through session observations. Acceptability will be measured using participant-reported perceptions of cultural relevance, perceived benefits, and overall satisfaction. Although Phase IIa is not designed to test efficacy, exploratory assessments of behavioral and biomedical outcomes will be conducted at baseline and 12 weeks post-intervention. Dietary adherence will be assessed using a multi-method approach combining the Perceived Dietary Adherence Questionnaire (PDAQ) adapted to the Benin Food Guide (53), dietary intake from the modified UKDDQ, and facilitator-rated behavioral monitoring (e.g., meal planning, food preparation, and physical activity practices) (51). Family functioning will be measured using the McMaster Family Assessment Device (54), diabetes knowledge using the ADKnowl questionnaire (55), and self-efficacy using the Diabetes Self-Efficacy Scale (DSES) (56). Anthropometric and clinical measures, including weight, height, waist circumference, blood pressure, and HbA1c—will also be collected with informed consent. Qualitative feedback from participants and facilitators will be analyzed to identify themes related to communication, comprehension, engagement, and perceived cultural relevance. Transportation incentives will be provided to facilitate participation in sessions and follow-up assessments.

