#### Phase IIb sample

2.4.1

A total of 60 adults with T2D will be enrolled and randomized in a 1:1 ratio to either the intervention group (OSanDiaBé) or a wait-list control group receiving usual care. Randomization will be conducted after screening and informed consent using a computer-generated randomization sequence. To minimize potential bias, the principal investigator will be aware of group allocation, while physicians, data collectors, and laboratory personnel will remain blinded. Participants will be informed of their group assignment following randomization. The target sample size (*n* = 60; 30 per group) is consistent with recommendations for pilot randomized trials and is intended to support intervention refinement and effect size estimation for subsequent efficacy studies (58). Findings from Phase IIa will further inform final sample size considerations for later trials.

Participants will be recruited from six collaborating health centers using provider referrals, peer referrals, flyers, and word-of-mouth outreach. Eligibility criteria include: self-identification as Beninese; age 40–65 years; a clinical diagnosis of T2D for ≥1 year; uncontrolled diabetes (HbA1c >7%); availability of a supportive family member; and ability to provide written informed consent. Participants must be deemed suitable for group-based education and general dietary and lifestyle guidance by the referring healthcare provider. Exclusion criteria include pregnancy, recent major cardiovascular events (e.g., stroke or congestive heart failure), clinical conditions requiring specialized dietary management, or current participation in a similar nutrition program, to minimize contamination and ensure participant safety.

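### In Phase IIb, the primary dietary adherence outcome includes facilitator ratings that have no described source in the control arm and are unblinded in the intervention arm

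*Protocol article*

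**What the plan says.** All references are to the Protocol article.

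- **Outcome.** Section 2.4.2 states the Phase IIb objective as "improving dietary adherence (primary behavioral outcome", with HbA1c as the primary biomedical outcome.
- **How it is measured.** The same section says "Dietary adherence will be assessed using a multi-method approach combining the PDAQ adapted to the Benin Food Guide", and adds "dietary intake from the modified UKDDQ, and facilitator-based behavioral monitoring, consistent with the Phase IIb measurement strategy". Outcome assessments apply to both groups at baseline and at 3, 6 and 12 months.
- **What the monitoring is.** Phase IIb does not describe it further. It cites the reference used in section 2.3.2 (Phase IIa), where facilitators score behaviour from 1 to 5 during the programme. That section calls it "facilitator-rated behavioral monitoring (e.g., meal planning, food preparation, and physical activity practices".
- **Contact with controls.** "Participants in the wait-list control group will complete assessment visits at baseline, 3 months, 6 months, and 12 months and will receive usual care". They are offered the programme, from the same facilitators, only after the 12-month assessment.
- **Contact with the intervention arm.** Sessions run in months 0 to 6. After that, "No intervention contact will occur between months 6 and 12".
- **Blinding.** Section 2.4.1 says that "physicians, data collectors, and laboratory personnel will remain blinded". Facilitators are not on that list.
- **Analysis.** Section 2.4.3 tests group-by-time interactions at baseline, 6 and 12 months, adjusts for the baseline value of each outcome, and uses multiple imputation as a sensitivity analysis.

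**The concern.** A randomised comparison needs the outcome to be obtained in the same way in both arms. Here one of the three sources of a primary outcome comes out of treatment delivery. A participant who is not treated has no facilitator to rate them, and a participant who is treated is rated by someone with a stake in the result.

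The same three-source definition appears in the single-arm Phase IIa, where no control comparison arises. It may have been carried into the randomised phase unchanged.

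Phase IIb is meant to supply effect estimates for later efficacy trials (section 2.4.1). A distorted adherence effect would therefore affect the planning of those trials as well as the pilot's own conclusion.

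**Working it through.** **No plan figure to reproduce.** The 60 participants (30 per group) are justified by a recommendation for pilot trials. No effect size, SD or power is given. The main check is to trace who could supply the facilitator rating, in which arm and when.

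| Visit | Intervention arm | Control arm |
|---|---|---|
| Month 0 | Conceivable: Table 2 marks an individual session | No described source |
| Month 3 | Available from sessions | No described source |
| Month 6 | Available from booster sessions | No described source |
| Month 12 | No described source: no intervention contact since month 6 | No described source |

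- Of 2 × 4 = 8 arm-by-visit cells, 4 + 1 = 5 have no described source.
- Of the 2 × 3 = 6 cells in the planned group-by-time analysis (months 0, 6, 12), 3 + 1 = 4 have none.
- At no visit is the component described for both arms.
- Month 12 is where the maintenance hypothesis of section 2.4 is tested. There the component is missing in both arms.
- The baseline adjustment in section 2.4.3 needs a baseline value in both arms. Controls have none for this component.
- Multiple imputation does not help. With no control ratings observed, the data hold nothing from which to estimate their distribution in that arm.

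**Illustration of the bias if controls were rated by some means.** None of the following inputs is in the document except 30 per arm and the 0.05 level (taken as two-sided).

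Assumptions: adherence is the equal-weight mean of three standardised components with common correlation r; there is no true effect; the facilitator component alone is inflated by b SD in the intervention arm; normal approximation.

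- SD of the mean = √(3 + 6r) / 3. For r = 0.4: √5.4 / 3 = 0.775.
- Spurious standardised difference d = (b/3) / SD. For b = 0.5: 0.1667 / 0.775 = 0.215.
- Standard error of d = √(2/30) = 0.258, so d/SE = 0.83.
- Rejection probability = Φ(0.83 − 1.96) + Φ(−0.83 − 1.96) = about 13.3%.

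| b (SD) | d for r from 0.6 to 0.2 | False-positive rate for r from 0.6 to 0.2 |
|---|---|---|
| 0.3 | 0.12 to 0.15 | 7% to 9% |
| 0.5 | 0.20 to 0.24 | 12% to 16% |
| 0.8 | 0.31 to 0.39 | 23% to 33% |
| 1.0 | 0.39 to 0.49 | 33% to 47% |

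For scale, 30 per arm has 80% power at d = (1.960 + 0.842) × 0.258 = about 0.72, without dropout.

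**The case against.** The strongest reply is that the article describes a multi-method approach and never says that the three sources form one score. The PDAQ and UKDDQ are scheduled for both arms at all four visits in Table 2, so dietary adherence can be compared on them as the plan stands. This is right, and it limits the point to comparisons that include the facilitator component. A reader might infer that the primary behavioural outcome cannot be compared between arms at all. The document does not support that.

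Other stronger readings also fail:

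- **That control ratings are impossible.** Nothing forbids a facilitator from rating a control at an assessment visit. But no such contact is described, and the rating would not be covered by the stated blinding. Facilitators also feature in the focus groups at 3, 6 and 12 months, but no rating is described there.
- **That the blinding statement is contradicted.** It covers physicians, data collectors and laboratory personnel. Facilitator ratings fall outside it and do not conflict with it.
- **That intervention participants are coached on UKDDQ items.** Phase IIa says "dietary intake will be assessed using the modified UK Diabetes and Diet Questionnaire (UKDDQ) to inform individualized nutrition prescriptions", but Phase IIb does not repeat this, and coaching on the items is stated nowhere.
- **That the lack of a named single score is an error.** Scoring and weighting may stand in an analysis plan that is not shown.
- **That the false-positive rate is a particular number.** The figures above follow from chosen inputs, presuppose control ratings that the plan does not describe, and model one two-group comparison instead of the planned repeated-measures ANOVA.

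It can also be said that this is a small pilot of preliminary efficacy. That lowers the stakes, but effect estimation is its stated purpose. An analysis plan cannot repair the matter later either, because it cannot recover ratings that were never taken or blind those already made.

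**Conclusion.** The point holds in a limited form. As described, the facilitator component of the Phase IIb adherence outcome has no source for 30 of 30 controls at any visit, and none for the intervention arm at month 12. Where it does exist, it is scored by treatment deliverers who know the allocation. Any between-arm adherence comparison that includes it is therefore non-comparable or biased.

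This rests on two readings. The first is that Phase IIb monitoring works as section 2.3.2 describes, since both sections cite the same reference. The second is that facilitator contact is limited to what section 2.4.2 sets out.

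The size of any bias cannot be derived from the document, and the ranges above are illustrative only.

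HbA1c, measured by blinded laboratory personnel, is unaffected. The PDAQ and UKDDQ do not have this defect, but both are self-reports by participants who are told their assignment, so some reporting bias would remain after the fix.

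**What to change.** In section 2.4.2, define the between-arm dietary adherence outcome only from instruments collected in the same way in both arms by the blinded data collectors: the PDAQ, the modified UKDDQ, or both. Naming the PDAQ as the primary score is one sound option, but the defect does not require that particular choice.

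State that facilitator ratings are reported only as a process or fidelity measure within the intervention arm, and in section 2.4.3 exclude them from the between-arm and group-by-time analyses. In the same edit, correct the reference to the Phase IIb measurement strategy, which at present points to its own phase.

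The cost is wording only, with no new measurement and no change to the 60 participants. The downside is one fewer component in the adherence measure. The change should be made before Phase IIb enrolment starts.

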#### Phase IIa sample

2.3.1

A single-arm feasibility design will be used to enroll 30 adults with T2D. Eligible participants will (1) self-identify as Beninese; (2) be aged 40–65 years; (3) have a clinical diagnosis of T2D for at least one year; (4) have an HbA1c level >7% at enrollment; (5) have a family member willing to participate or provide ongoing support; and (6) be willing to commit to the study protocol and attend scheduled sessions. Participants will be recruited from the pool of 512 individuals who participated in Phase Ib. The sample size of 30 was selected in accordance with recommendations for pre-pilot and feasibility studies (43). The intervention will include two individual sessions (45–60 min each) and eight group sessions (90–120 min each). Sessions will be delivered by six trained dietitians or nutritionists, with each group of 10 participants assigned two facilitators experienced in health promotion, trained in MNT, and committed to maintaining protocol fidelity.

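### One component of the Phase IIb primary behavioral outcome comes from the unblinded facilitators who deliver the intervention, and cannot validly enter a between-arm comparison

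*Protocol article*

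**What the plan says.** All references are to the protocol article.

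- **Outcome.** Section 2.4.2 (Phase IIb procedures) sets the primary objective as preliminary efficacy in "improving dietary adherence (primary behavioral outcome), and glycemic control (HbA1c) (primary biomedical outcome").
- **Measurement.** The same section says adherence is assessed by combining the PDAQ adapted to the Benin Food Guide, "dietary intake from the modified UKDDQ, and facilitator-based behavioral monitoring". The sentence before it reads: "Outcome assessments for both groups will be conducted at baseline and at 3, 6, and 12 months".
- **What the third component is.** The Phase IIa text (section 2.3.2) calls it "facilitator-rated behavioral monitoring (e.g., meal planning, food preparation, and physical activity practices") and describes facilitators monitoring behavior throughout the intervention, "using a standardized adherence scale ranging from 1 (never) to 5 (consistently"). Both phases cite the same source for it, reference 51.
- **Who facilitators are.** In Phase IIa, "Sessions will be delivered by six trained dietitians or nutritionists, with each group of 10 participants assigned two facilitators". For Phase IIb, section 2.4.2 says that after the 12-month assessment controls "they will be offered the OSanDiaBé intervention delivered by the same trained facilitators to ensure equitable access".
- **Blinding.** Section 2.4.1 has the principal investigator aware of allocation, "while physicians, data collectors, and laboratory personnel will remain blinded". Participants are told their assignment. Facilitators are not mentioned.
- **Contact.** Until the 12-month assessment, controls receive usual care and attend assessment visits. The intervention arm has no intervention contact between months 6 and 12.

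**The concern.** A randomized comparison needs each component of its outcome to be obtained in the same way in both arms, preferably by someone who does not know the allocation. The facilitator component does not meet that standard. The people scoring it run the sessions, know who attends them, and are judging the result of their own teaching. The article describes no setting in which they would observe a control participant during the 12 months of follow-up.

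Preliminary efficacy on adherence is part of the stated primary objective. The pilot is also meant to supply effect sizes for later efficacy studies. A difference created by the measurement would be read as a signal of benefit and carried into the planning of the next trial.

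**Working it through.** **Step 1. Set the passages side by side.**

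| Element | Intervention arm | Control arm |
|---|---|---|
| Facilitator contact, months 0-6 | Four individual and eight group sessions | None described |
| Facilitator contact, months 6-12 | No intervention contact | None described |
| Adherence assessment | 0, 3, 6, 12 months | 0, 3, 6, 12 months |
| Blinded data collectors | Yes | Yes |
| Blinded facilitators | Not claimed, and not possible for those running sessions | Not claimed |

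**Step 2. Two possible readings.**

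(a) Facilitators also rate controls. They do so knowing that these people did not attend sessions, so a leniency or expectation shift enters the between-arm difference.

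(b) Facilitators rate only the intervention arm. There is then no control value. Rater expectation cannot bias a between-arm contrast on this component because no such contrast exists. But an adherence measure that includes the component is built differently in the two arms.

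The article does not say which applies. The contact pattern points more toward (b). Under neither reading is the component comparable between arms.

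**Step 3. Illustration of size, for reading (a) only.** The article gives no power calculation to reproduce: 60 participants (30 per group) rests on pilot-trial recommendations.

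Inputs from the article: 30 per arm; significance at P < 0.05 (taken as two-sided).

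Assumptions not in the article: controls are rated; the three components are standardized and averaged with equal weight; their pairwise correlation r is 0.3 or 0.5; there is no true effect; the facilitator component is shifted by s SD in one arm; and one two-sample t-test is done at a single follow-up.

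- Composite SD = sqrt((3 + 6r)/9). For r = 0.3 this is sqrt(4.8/9) = 0.730. For r = 0.5 it is sqrt(6/9) = 0.816.
- Shift in composite SD units: d = (s/3) / composite SD.
- Standard error of the difference in SD units = sqrt(2/30) = 0.258.
- Non-centrality = d/0.258. The rejection probability comes from the non-central t with 58 degrees of freedom, both tails, critical value 2.002.

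| r | s | d | d/0.258 | False-positive rate |
|---|---|---|---|---|
| any | 0 | 0 | 0 | 5.0% |
| 0.3 | 0.5 | 0.228 | 0.88 | 14.0% |
| 0.3 | 1.0 | 0.456 | 1.77 | 41.2% |
| 0.5 | 0.5 | 0.204 | 0.79 | 12.2% |
| 0.5 | 1.0 | 0.408 | 1.58 | 34.3% |

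A smaller shift of 0.25 SD at r = 0.3 gives about 7%. The result is sensitive to the assumed shift, and the article gives no basis for choosing one.

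**The case against.** **A reader might infer that the article contradicts itself on blinding.** It does not. Section 2.4.1 lists physicians, data collectors and laboratory personnel as blinded. It neither lists facilitators nor calls them data collectors. What stands is narrower: the stated safeguard does not reach one named source of a primary outcome.

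**A reader might infer that rater expectation will produce a false adherence effect at the rates tabulated.** The article does not support that either. No passage describes facilitators rating controls, and none defines a numeric composite or its weights. The three sources could be reported side by side, and a condensed article may leave scoring to a fuller document. The analysis in section 2.4.3 also includes baseline-adjusted repeated-measures ANOVA, which the single t-test in the illustration does not represent. The percentages show what could happen under stated assumptions; they do not estimate this trial's error rate.

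**The Phase IIb wording is thinner than the Phase IIa wording.** The 1-to-5 scale and the description of the component as rated by facilitators come from the single-arm Phase IIa text. However, the Phase IIb text cites the same source and introduces no other rater, so the natural reading is that the measure carries over.

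**It is a pilot, and participants are unblinded anyway.** Both are true, and they temper the severity. But the pilot has a comparative hypothesis and between-group tests, and is to inform effect sizes. Participant awareness of allocation is inherent in this design; having the deliverers score the outcome is not.

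A fuller document could settle the weighting. It could not blind a facilitator to who attends their sessions.

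**Conclusion.** The point holds in limited form and should be fixed. As written, part of the Phase IIb primary behavioral outcome is supplied by unblinded deliverers of the intervention. It is either rated with knowledge of allocation or absent in the control arm, and in both cases it is unsuitable for the between-arm comparison. That conclusion needs no numerical assumption beyond reading the Phase IIb monitoring as the same measure described for Phase IIa.

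The size of any bias cannot be determined from the article. The illustrative rise from 5% to about 12-14% (0.5 SD shift) or 34-41% (1.0 SD shift) applies only if controls are rated and the components are averaged as assumed. HbA1c, the primary biomedical outcome, is a laboratory measure handled by blinded personnel and is not affected.

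**What to change.** In section 2.4.2, define the between-arm dietary adherence outcome from the PDAQ and modified UKDDQ only, and state that the blinded data collectors obtain both in the same way in both arms at every assessment. Remove facilitator-based monitoring from that outcome. Report it descriptively in the intervention arm as a process and fidelity measure.

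Add a limitation: both remaining instruments are answered by participants who know their allocation, so blinded collection does not remove reporting bias.

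The cost is a change of wording before Phase IIb starts. The multi-method outcome loses one component, but the facilitator ratings are still collected and reported. The sample size, visits and intervention do not change.
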